## Methods

### Design

To examine the relevance of kinesthesia for treatment and diagnosis of depression, we aim to conduct a four-armed, parallel, single-blind RCT (see Fig. 2) in accordance with the CONSORT statement [36]. The study is preregistered in the Open Science Framework (https://osf.io/mswfg/). It will be carried out at the EmpkinS Lab of the Friedrich-Alexander-Universität Erlangen-Nürnberg, structured around a smartphone-based training. There will be three intervention conditions: (1) a cognitive reappraisal training (CR), (2) CR enhanced by instructions to deliberately display anti-depressive facial expressions (CR + AFE), and (3) facial muscle training focusing on anti-depressive facial expressions (AFE). The control condition (4) will receive a sham intervention. Participants will be randomly allocated to one of the four study conditions with a 1:1 allocation ratio. A block randomization with a randomly varying block size of four or eight will be performed following a randomization list generated using the blockrand-package in R Studio [37]. To control for confounding expectation effects, participants will be blinded regarding the study condition they are allocated to, but will be debriefed after study completion. Moreover, to avoid biased assessments, researchers conducting the follow-up assessment will also be blinded to participants’ group allocation.

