### Participants

We will recruit two participant groups of equal size with differing diagnostic status: one group of individuals with clinically relevant depressive symptomatology and a control group of individuals without depression. The diagnostic groups will be matched according to gender and age. For the depression group, the main inclusion criterion is the presence of a diagnosis from the depressive spectrum according to ICD-10 criteria (F32 ‘depressive episode’, F33 ‘recurrent depressive disorder’, F34.1 ‘dysthymia’, and F43.20 & F43.21 ‘adjustment disorder with depressive symptoms’ [38]) according to the Structured Clinical Interview for DSM-5 Disorders - Clinician version (SCID-5-CV; German Version: [39]). The main inclusion criterion for the group without depression is a score < 10 on the Patient Health Questionnaire (PHQ)-8 [40]. Additional inclusion criteria for both groups include being ≥ 18 years, being able and willing to provide informed consent regarding study participation, and having sufficient German language skills (at least level B2 according to the Common European Framework of Reference for Languages). Exclusion criteria included the presence of any psychotic disorder (ICD-10 F2x), any substance dependence disorder other than nicotine (ICD-10 F1x.2), acute suicidality, any impairment of facial expression (e.g., due to facial paralysis or recent Botox treatment or autism spectrum disorder), and any type of dyschromatopsia. To ensure maximum external validity, we refrain from applying further potential exclusion criteria such as other clinical comorbidities, or concurrent pharmaco- or psychotherapy, but will record this information.

A power analysis was conducted with G*Power [41] to determine the necessary sample size for a 2-group-comparison of each of the intervention conditions (CR, CR + AFE, AFE) with the sham control condition. In absence of similar studies serving as reference for the determination of a critical effect, a team of three clinical experts agreed that an effect size of *d* = 0.5 would be therapeutically relevant. The power analysis yielded a necessary sample size of *n* = 32 for each of the four intervention conditions and two diagnostic groups based on a 2-sided analysis, a critical alpha-level of α = 0.05, and a power of β = 0.80. Hence, we will include *N* = 256 participants in total, composed in equal parts of participants with depression (*n* = 128) and without depression (*n* = 128).

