### Statistical analysis plan

Analyses will be conducted via SPSS Version 29 for Windows [61] and R Studio [37]. While analyses will focus on a per-protocol approach, intention-to-treat-analyses using imputations for missing data will also be conducted. In accordance with the CONSORT statement [36], number and reasons for dropout will be recorded and reported for each condition.

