#### Efficacy of the reappraisal training augmented with facial expressions

In order to study the effectiveness of the EmpkinS-EKSpression app-based interventions, generalized linear models (GLMs) of the between-subject factors “diagnostic group” (with depression vs. without depression) and “intervention condition” (CR vs. CR + AFE vs. AFE vs. sham control), as well as the within-subject factor “time of assessment” will be applied in a stepwise fashion.

Regarding the primary outcome of depressed mood, we will first examine whether the mood induction phase *induces* depressed mood using a paired *t*-test with the pre- and post-mood-ratings as dependent variable (manipulation check). Further, hierarchical linear models (HLMs) will be implemented to assess whether the EmpkinS-EKSpression app-based interventions are effective in *reducing* depressed mood. As a first step, we will compare the CR condition with the sham control condition and the CR + AFE with the CR condition to study whether cognitive reappraisal training can be augmented with anti-depressive kinesthesia. As a second step, we will compare the AFE condition with the sham control condition. For continuously assessed secondary outcomes (i.e., positive mood, app data), corresponding analyses will be conducted.

With regard to secondary outcomes (i.e., GRID-HAMD, CES-D, current suicidality, ERSQ-ES, DAS-A, ATQ-R) assessed at pre-treatment, post-treatment, and/or follow-up, as well as pre/post mood-ratings, we will implement mixed analyses of variance (ANOVAs), again with the between-subject-factor, “study condition” (CR, CR + AFE, AFE, sham control) and the within-subject factor, “time.” Feasibility measures (treatment integrity, compliance, usability, acceptability) will be descriptively analyzed and contrasted between study conditions utilizing one-way ANOVAs. Finally, changes in kinesthesia and other psychophysiological measures over the course of the intervention, as well as differences between diagnostic groups and intervention conditions will be examined using, again, HLMs. All analyses will be conducted using the whole sample, as well as with the added between-subject-factor, “diagnostic group” (with vs. without depression). All analyses will be conducted with a significance level of α = 0.05. One-tailed tests will be used when the algebraic sign of the test statistic is specified; otherwise, two-tailed tests will be used.

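### The stated 80% power belongs to 64 against 64 participants pooled over diagnosis, but the text attaches it to 32 per condition within each diagnostic group, where the same calculation gives about 50%

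*Protocol article*

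**What the plan says.** The Participants section of the protocol article describes a power analysis for a "2-group-comparison of each of the intervention conditions (CR, CR + AFE, AFE) with the sham control condition". Three clinical experts agreed that d = 0.5 "would be therapeutically relevant". The error rates are given as "a critical alpha-level of α = 0.05, and a power of β = 0.80", where the second figure is evidently the power. The result is n = 32 "for each of the four intervention conditions and two diagnostic groups based on a 2-sided analysis", and from this the section derives N = 256, "composed in equal parts of participants with depression" (128) and without (128). The Design section adds that participants are "randomly allocated to one of the four study conditions with a 1:1 allocation ratio".

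The section on efficacy of the augmented reappraisal training describes how diagnosis enters the analysis: "All analyses will be conducted using the whole sample, as well as with the added between-subject-factor" for diagnostic group. It also allows one-tailed tests where a direction is specified. The opening of the Statistical analysis plan section says: "While analyses will focus on a per-protocol approach", with intention-to-treat analyses run as well.

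**The concern.** Read as written, the sentence promises 80% power with 32 participants per condition inside each diagnostic group. A two-group comparison at d = 0.5 needs twice that number.

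This matters because the article's aim covers people with and without depression, and its Discussion is about improving reappraisal in depression and possible use as a treatment for it. Many readers will therefore look first at the effect in the depression group. Someone who takes the power sentence at face value would read a null result there as coming from an 80%-powered comparison, when the article's own inputs give about an even chance of detecting the target effect.

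**Working it through.** **Inputs from the article.** Two-group comparison of means; d = 0.5 (so SD = 1); two-sided alpha 0.05; power 0.80; equal allocation; 32 per condition and diagnostic group, hence 32 + 32 = 64 per condition over both groups.

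**1. Reproducing the plan's figure.** Normal approximation, per group:

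n = 2 × ((1.960 + 0.842) / 0.5)² ≈ 62.8, so 63.

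The exact t calculation (noncentral t) gives 64. Then 4 × 64 = 256, which is the stated N. The figure reproduces on the pooled reading.

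**2. Power at the two sample sizes.** The noncentrality is d × √(n/2), with 2n − 2 degrees of freedom.

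| Comparison | Noncentrality | Power, two-sided | Power, one-tailed |
|---|---|---|---|
| 64 v 64 (pooled) | 0.5 × √32 = 2.83 | 0.801 | 0.879 |
| 32 v 32 (one diagnostic group) | 0.5 × √16 = 2.00 | 0.504 | 0.631 |

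The two-sided critical value at 32 v 32 is about 2.00, equal to the noncentrality, so power is about one half.

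**3. Could another reading give 32?** A one-tailed test still needs 51 per group. A paired t-test needs 34, which is close, but it is not the between-condition comparison described.

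**4. Smallest effect detectable with 80% power at 32 v 32, two-sided.** d ≈ 0.71.

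**5. Diagnosis-by-condition contrast.** For a difference in effects of 0.5 SD with 32 in each of four cells, the standard error is √(4/32) = 0.354. The noncentrality is 0.5 / 0.354 = 1.41, and power is about 0.29.

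**6. Effect of leaving diagnosis out of the pooled model.** Assume that the two diagnostic groups' means on the outcome differ by 1 within-group SD; the article gives no figure. Mixing equal halves adds 0.5² = 0.25 to the variance, so the effective d is 0.5 / √1.25 = 0.447. At 64 v 64 the noncentrality is 0.447 × √32 = 2.53, and power is about 0.71. With diagnosis in the model this loss does not arise.

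**The case against.** The strongest reply is that nothing has been miscalculated. The comparison named is condition against sham, not condition against sham within a diagnosis. On that reading 32 is simply the cell size of a four-by-two layout, the whole-sample analysis is listed first, and it has the 80% claimed. No depression-only test is defined, the aim covers people with and without depression, and the Discussion presents the study as a proof of principle.

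Most of this stands. A reader might infer that N = 256 is wrong, or that the depression group should be doubled. The documents do not support that, because the planned pooled comparison is adequately sized on its own assumptions.

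A reader might also take 50% as the trial's actual power in depression. That goes too far. It is the figure for a simple two-sample t-test, whereas the primary analysis is a hierarchical model of up to 96 mood ratings per person. If a baseline covariate correlated about 0.71 with the outcome, an adjusted 32 v 32 comparison would reach about 80%. That correlation is an assumption. The article neither states one nor uses one in its power analysis.

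Two further scenarios rest on assumptions alone. If the effect existed only in depressed participants, pooled d would be 0.25 and pooled power about 0.29. If about 10% were excluded per protocol (58 per condition), pooled power would be 0.76. The article gives no basis for either, and the primary outcome is collected within one supervised session. Low interaction power is also common and contradicts nothing, since no power is claimed for it.

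What the reply does not remove is the sentence itself. It ties the 80% to 32 per condition and diagnostic group and omits the pooling on which the figure depends.

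**Conclusion.** The point holds as a misstatement of what the sample size delivers, not as an error in N. The 80% is correct for 64 v 64 pooled over diagnosis, provided that d = 0.5 applies in both diagnostic groups, nobody is lost from the analysis, and differences between the diagnostic groups do not inflate the residual variance. For one diagnostic group the same calculation gives about 0.50 two-sided, or 0.63 one-tailed, so the permitted one-tailed tests do not close the gap. These figures use only the article's inputs and a simple t-test. The 0.71 for an unadjusted pooled comparison depends on the assumed 1 SD difference. This should be fixed, but it does not threaten the design.

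**What to change.** Restate the power paragraph along these lines:

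- Sixty-four participants per condition, pooled over diagnostic groups, give 80% power for a common d = 0.5 (two-sided 0.05, no losses).
- The comparison for which the trial is sized is the pooled one with diagnostic group in the model.
- Within the depression group, 32 per condition give about 50% power by the same calculation, with a detectable d of about 0.71. Effects there will be reported as estimates with confidence intervals.
- The diagnosis-by-condition interaction is exploratory (about 0.29 power for a 0.5 SD difference in effects).

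If the authors expect the repeated ratings to raise power, they should state the correlation they assume and show the resulting figure. Any per-protocol exclusion rate or depressed-only effect that is mentioned should be labelled an assumption.

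The cost is wording and a less favourable figure for the depression group. N stays at 256.

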### Procedure

Recruitment will take place via newspaper and social media advertisements, mailing lists, and flyers on public bulletin boards. Furthermore, individuals with depression will be recruited via the outpatient clinic for psychotherapy of the Friedrich-Alexander-Universität Erlangen-Nürnberg, and by contacting psychiatric or psychosomatic clinics, counselling center, psychotherapists, and general practitioners in and around Erlangen via telephone or email.

The recruitment material will provide a QR code and link to the study website hosted by Unipark.com. Here, interested individuals will find extensive information on study aims and procedures (without jeopardizing blinding). Furthermore, they will be able to directly access the study screening questionnaire (T0) on demographic information, inclusion and exclusion criteria, and symptoms of depression. If eligible, participants will be invited to a first appointment in the laboratory for a diagnostic session (T1). During this session, after obtaining written informed consent, two diagnostic interviews (see Table 1) will be conducted by trained psychologists. All interviews will be video-recorded and 10% rated by a second expert to determine inter-rater reliability for diagnostic status. In case of ambiguity, the diagnostic status will be deliberated with experienced clinical psychologists. Moreover, participants will answer a set of questionnaires delivered on a computer tablet via Unipark.

**Table 1 Tab1:** *Overview of measures per Time Point*

Variable	Instrument	Time point					
		T0	T1	T2	Continuous^a^	T3	T4
**Screening**							
Demographic information	self-developed	X					
Health-related information	self-developed	X					
Symptoms of depression	PHQ-8/-9	X	X				
**Diagnostic interviews**							
Clinical status	SCID-5-CV		X				
Symptoms of depression	GRID-HAMD		X				X
**Psychometric measures**							
*Primary outcome*							
Current depressed mood	self-developed		X		X		
*Secondary outcomes*							
Current positive mood	self-developed		X		X		
Symptoms of depression	CES-D			X			X
Current suicidality	self-developed		X	X		X	X
Emotional state	ERSQ-ES A		X				X
Dysfunctional attitudes	DAS-A		X				X
Automatic thoughts	ATQ-R		X				X
**Feasibility measures**							
Treatment integrity	RGB camera		X		X		
	self-developed		X		X		
Compliance	self-developed				X		
Usability	UEQ-S					X	
	self-developed					X	
Acceptability	UEQ-S					X	
	self-developed				X	X	
**Kinesthesia**							
Facial expression/body posture	RGB camera		X^b^		X		
	Azure Kinect depth camera				X		
	Smartphone camera				X		
**Further psychophysiological measures**							
Facial muscle activity^c^	Biopac MP160				X		
Respiration rate (variability)	Biopac MP160				X		
Heart rate (variability)	Biopac MP160				X		
	24 GHz & 61 GHz CW Radar systems (self-developed)				X		
Verbal acoustics	Microphone		X		X		
**Technical app data (e.g.**,** reaction time**,** item choice**,** credibility of emotion display)**	EmpkinS EKSpression app				X		

Note. T0 = Screening; T1 = diagnostic session one week before the training; T2 = assessment directly before the training; T3 = assessment directly after training completion; T4 = assessment two weeks after training completion. SCID-5-CV = Structured Clinical Interview for DSM-5 Disorders Clinician version; GRID-HAMD = GRID Hamilton Rating Scale for Depression; PHQ-8/-9 = Patient Health Questionnaire-8/-9; CES-D = Centre for Epidemiological Studies Depression Scale; DAS-A = Dysfunctional Attitude Scale version A; ATQ-R = Automatic Thoughts Questionnaire-Revised; ERSQ-ES A = part A of the Self-Report Instrument for the Assessment of Emotion-Specific Regulation Skills; UEQ-S = User Experience Questionnaire, short version

^a^Measures are taken continuously during the training. ^b^The main purpose of the video recordings during T1 was to determine inter-rater reliability of the diagnostic interviews. ^c^We will use a bipolar electromyogram to measure activity of the musculus corrugator supercilii, musculus zygomaticus major, musculus masseter (only in the AFE condition), and musculus orbicularis oculi

The training session will take place one week after the diagnostic session at the laboratory, taking approximately three hours in total. At the beginning, participants will be randomly allocated to study conditions. We will use numbered, sealed envelopes containing the respective allocation information. The envelopes will be prepared by a student assistant not otherwise involved in the study. Following a pre-assessment (T2) on a computer tablet via Unipark.com and the setup of the kinesthetic and physiological data acquisition (see below for details), participants will receive brief psychoeducational instructions about the interconnection of cognitions (thoughts), the body (e.g., facial expression) and emotion/mood. Then, they will complete the 90-120-minute intervention on a study smartphone. The training session will be concluded with a brief self-report post-assessment (T3).

Two weeks after the training session, a follow-up assessment (T4) will take place in the form of a telephone interview to reassess the severity of depressive symptoms using the Hamilton Rating Scale for Depression (HAMD). Additionally, participants will be asked to complete online questionnaires via Unipark.com, which they will receive via email one day before the telephone interview. Figure 2 outlines the study procedures. Participants will receive compensation in the amount of €40 up to €100 for individuals with depression in the final phase of the study, whereby psychology students will have the option to receive course credits instead of financial reimbursement. Further, individuals with any current psychiatric disorder according to the SCID-5-CV are offered priority on the waitlist of the outpatient clinic for psychotherapy of the Friedrich-Alexander-Universität Erlangen-Nürnberg.

All study sessions will be conducted by study therapists holding at least a bachelor’s degree in Psychology. They will be trained and supervised by clinical psychologists, and a trained and licensed CBT psychotherapist will be accessible by phone at all times. Moreover, all training procedures will be manualized to ensure best practice on the side of the study therapists.

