#### Secondary outcomes

Similarly to current depressed mood, *current positive mood* will be assessed by means of an eleven-point Likert-scale from 0 to 10, with 0 = *no positive mood at all* and 10 = *very strong positive mood*, respectively. The number of mood ratings for positive mood is the same as for depressed mood, adding up to a total of 96 positive mood ratings over the course of the training.

Beyond clinical interviews and single-item mood ratings, questionnaires will be administered at several points during the training. The German version of the Centre for Epidemiological Studies Depression Scale (CES-D; [53]) will be administered to assess self-reported symptoms of depression during the previous week. The 20 items are rated on a four-point Likert scale from 0 (*some of the time*) to 3 (*most of the time*). A total score can be obtained by summing up the items, with a score greater than 22 considered to be clinically relevant [53]. The CES-D has demonstrated good reliability and validity in several studies [54, 55].

*Current suicidality* will be assessed with a single, self-developed item on a six-point Likert scale from 1 (*no suicidality*) to 6 (*suicide attempt*).

*Emotional state* will be assessed with Part A of the Self-Report Instrument for the Assessment of Emotion-Specific Regulation Skills (ERSQ-ES; [56]). This scale measures feelings and mood during the previous week with 50 items on a 5-point Likert scale from 0 (*never*) to 4 (*all the time*). *Dysfunctional attitudes* will be assessed with the German short version of the Dysfunctional Attitude Scale version A (DAS-18-A; [57]). The short version consists of 18 items assessing respondents’ agreement with dysfunctional attitudes that are typically found among individuals with depression (e.g., “My value as a person depends on what others think of me”) during the last week on a 7-point Likert scale from 1 (*fully disagree*) to 7 (*fully agree*). The DAS-18-A has shown good validity and reliability in patients with depressive symptoms and in healthy individuals [57].

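### Allocation at the start of the training visit comes before the T2 assessment, so anyone who stops at T2 is a randomised loss and the only CES-D baseline is taken after allocation

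*Protocol article*

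**What the plan says.** The Procedure section (text after Table 1) describes one training visit, a week after the diagnostic session T1. It opens with allocation by numbered, sealed envelope: "At the beginning, participants will be randomly allocated to study conditions". The next step reads "Following a pre-assessment (T2) on a computer tablet via Unipark.com and the setup of the kinesthetic and physiological data acquisition", after which come psychoeducation and the smartphone training. The note to Table 1 defines T2 only by its timing: "T2 = assessment directly before the training".

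Table 1 lists the suicidality item at T1, T2, T3 and T4, and the CES-D at T2 and T4 only. Under Participants, the exclusion criteria include "acute suicidality, any impairment of facial expression". Under Secondary outcomes, current suicidality "will be assessed with a single, self-developed item on a six-point Likert scale from 1" (no suicidality) to 6 (suicide attempt), with no cut-off linked to the exclusion criterion.

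The Design section blinds participants and the researchers who do the follow-up assessment. It does not say that the staff who run the training visit are blinded. The Statistical analysis plan section states: "While analyses will focus on a per-protocol approach". The same sentence adds an intention-to-treat analysis with imputation, and the next one promises that the number of dropouts and their reasons will be reported for each condition.

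**The concern.** Allocation is best placed after the last measurement that could lead someone not to go on, and after all baseline data. Here it comes before both, although T2 and allocation take place in the same visit.

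Two things follow. First, a participant who stops between T2 and the training counts as a randomised dropout, where the reverse order would have made that person a screen failure. Such losses are unlikely to be random with respect to depressed mood, which is the primary outcome. Second, the CES-D has no baseline that precedes allocation. The first consequence matters more, because the plan gives priority to a per-protocol analysis, which does not keep everyone who was randomised.

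**Working it through.** The point concerns the order of procedures, so most of the check sets places in the article side by side.

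1. **Order within the visit.** Procedure: allocation, then T2, then sensor set-up, then psychoeducation, then training. Smartphone-based intervention: the training opens with a preparatory phase, followed by an induction of depressed mood. T2 is therefore the last questionnaire assessment before the induction, and it follows allocation.

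2. **What is known before allocation.** Procedure places screening on the inclusion and exclusion criteria at T0 and the diagnostic interviews at T1. The Measures section says that suicidality was assessed only face-to-face, so the online screening at T0 cannot settle that criterion. The reading available at allocation is the one from T1, a week old.

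3. **Who knows the arm.** Study therapists conduct all sessions (Procedure), give the condition-specific instructions and operate the app (Smartphone-based intervention). The article does not say who opens the envelope. The therapist may therefore know the arm while T2 is completed. The participant is blinded.

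4. **What a person lost at T2 contributes.** Primary outcome: all 96 ratings of depressed mood come from the smartphone session. Someone who stops at T2 has none of them; only the T1 mood rating in Table 1 remains. The article does not define the per-protocol set, but a person who never starts the training would ordinarily fall outside it. The intention-to-treat analysis would have to impute the in-session ratings.

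5. **Which baselines are affected.** GRID-HAMD, DAS-A, ATQ-R and ERSQ-ES all have a T1 value before allocation. Only the CES-D has its sole baseline at T2.

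6. **The plan's sample size.** Inputs from Participants: d = 0.5, two-sided alpha 0.05, power 0.80. A two-sample t-test needs 63.77, so 64 per condition, and 4 × 64 = 256, which is the stated total. This reproduces only if the 32 depressed and 32 non-depressed participants of each condition are pooled. Power at 64 per condition is 0.801.

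7. **Size of a loss at T2.** The article gives no rate, so the rates below are assumptions, with the loss spread equally over the conditions. Number lost = 256 × rate; remaining per condition = 64 × (1 − rate).

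| Assumed loss | Participants lost | Left per condition | Power |
|---|---|---|---|
| 0% | 0 | 64 | 0.801 |
| 1% | 2.56 | 63.36 | 0.797 |
| 2% | 5.12 | 62.72 | 0.793 |
| 5% | 12.8 | 60.8 | 0.781 |
| 10% | 25.6 | 57.6 | 0.758 |

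If only depressed participants were affected, at an assumed 1% to 4%, the loss would be 128 × 0.01 = 1.28 to 128 × 0.04 = 5.12 people in all. That is 0.32 to 1.28 per condition, out of 32. The documents do not allow an estimate of the bias from a loss that differs by arm.

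**The case against.** The strongest objection is that T2 is not an eligibility gate. A reader might infer from the exclusion criterion and the T2 suicidality item that participants are excluded at T2 with their arm known. The article does not support this. Eligibility sits at T0 and T1, suicidality is already measured at T1, the item is a secondary outcome repeated at T3 and T4, and no exclusion on T2 data is described. This stands: a post-randomisation loss at T2 is a risk created by the order, not a stated procedure. Nor is it a finding that the article fails to mention a renewed eligibility check, since a condensed article can leave such detail to the full protocol. The order of the visit, however, is stated.

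A reader might also infer that the CES-D baseline is biased because staff who know the arm collect it. That does not hold either. It is self-report on a tablet by blinded participants about the previous week, completed before any arm-specific content, and the primary outcome does not use it. What stands is that it is collected after allocation without need.

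The plan also has safeguards: an intention-to-treat analysis and dropout reporting by condition. They limit the harm but do not remove it, because the stated focus is per-protocol and the in-session outcome would have to be imputed.

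Finally, recruitment began in January 2023 and was expected to end in January 2025, so a change of order may reach few participants. This stands and shapes the fix.

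**Conclusion.** The point holds as a matter of order. Allocation precedes T2, although nothing in T2 depends on the allocation. Anyone who does not continue after T2 becomes a randomised loss, with the arm possibly known to the session therapist, without in-session primary-outcome ratings, and outside the analysis on which the plan focuses. The CES-D baseline follows allocation, with little likely bias.

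The size is unknown and probably small. At the assumed equal losses of 1% to 10%, power falls by 0.4 to 4.3 percentage points. The concern is selective loss more than lost power. The conclusion rests on reading the Procedure text in its written order and on the session therapist being unblinded, which the article implies but does not state.

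**What to change.** Change the order within the same visit: complete the T2 tablet assessment, then open the envelope, then set up the sensors. Sensor set-up has to stay after allocation, because masseter EMG is used only in the AFE condition and EMG is applied to all AFE participants but to half of those in the other conditions. All questionnaire baselines then precede allocation, and anyone who does not continue after T2 is a screen failure before randomisation. The sample size stays at 256.

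For participants already enrolled under the current order, keep T2-stage losses in the intention-to-treat set and report their number and reasons by arm.

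The cost is a short pause in which someone checks T2 before the envelope is opened. No further assessment or visit is needed. How a T2 response is handled clinically is for the clinical team; the Participants section, Table 1 and the Procedure section need only be reconciled on timing.
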